### Postoperative management

After surgery, patients will be taken to the recovery room and monitored according to standard hospital policy before return to the transplant ward for post-operative care.

Patients will receive their normal medications prior to surgery unless otherwise directed by the anaesthetist.

### Criteria for discontinuation

Every effort will be made to retain patients in the trial and to minimise withdrawals. Patients with capacity to consent may request to be withdrawn from this study at any time. If the patient develops a severe or life-threatening condition and loses capacity, continued consent will be presumed unless it is deemed that continuation of the trial will result in an adverse outcome for the patient. This is because follow-up of patients who have complications is particularly important for this trial, as it is examining the effect that preoperative intravenous fluid has on these.

In patients who do withdraw from the study, reasons for withdrawal will be documented. All data accumulated up to the time of withdrawal will be retained and included in subsequent statistical analyses.

### Study Centre

The study will be conducted solely within the West of Scotland Renal Transplant Unit. Follow-up will be undertaken in out-patient clinics throughout NHS Greater Glasgow and Clyde by the Renal Transplantation Team.

### Data Collection

Data will be obtained from the ward observation and fluid charts, anaesthetic record, recovery room observation chart, laboratory and bedside blood test results, intraoperative data collection and clinical review in the post-operative period. To avoid any bias, the outcome assessor will be blinded to the fluid hydration that the patient received. The data that will be collected includes demographic data, patient details, perioperative details and primary and secondary outcome data [Table 1].

**Table 1 Tab1:** Data to be collected

Donor and Recipient Demographic Data	Age Gender Ethnicity Weight Body mass index
Recipient Details	Comorbidities Indication for transplant
Perioperative Details	Volume of donor fluid intake—oral and intravenous Preoperative donor urine output Intraoperative donor urine output Donor fluid boluses and response to fluid challenge. Surgeon performing the operation Duration of surgery Cold and warm ischaemic times
Primary and Secondary Outcome Data	Donor NGAL and BNP (4 measurements): preoperative (day −1), immediately preoperative (day 0), immediately postoperative (day 0), postoperative (day +1) Recipient NGAL (3 measurements): preoperative (baseline), immediately post-operative, postoperative (day +1). Donor eGFR: days 1–4, week 6 and 1 year Recipient eGFR: week 6 and 1 year Recipient delayed graft function (DGF)—defined as use of dialysis in the first week postoperatively 1 year graft and patient survival in recipient Donor intraoperative haemodynamics (including blood pressure, heart rate, stroke volume index, cardiac index and systemic vascular resistance). Biomarkers of AKI, including N-GAL, KIM-1 and leukocyte subsets, in blood obtained from renal vein during retrieval and implantation surgery Donor and recipient perioperative mortality Donor and recipient perioperative complications (including cardiorespiratory complications, time to first bowel motion, infective complications, length of hospital stay, readmission)

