### Pilot Data

Pilot data obtained at our study centre involving 20 donors indicate that hand-assisted laparoscopic nephrectomy is associated with significant subclinical acute kidney injury, defined as plasma NGAL >153 ng/ml, and that preoperative fluids may reduce the incidence of this. In a non-randomised pilot series, where fluids were administered as per surgeon preference, there was found to be an incidence of subclinical acute kidney injury of approximately 50% in patients receiving <1000 ml of intravenous fluids compared with a 20% incidence in those receiving >2500 ml of intravenous fluids. An inverse correlation between increase in NGAL and post donation eGFR at 6 weeks was also demonstrated [31].

The risk of subclinical acute kidney injury has been demonstrated by Hasse et al. who analysed pooled data from ten prospective observational studies, involving over 2000 patients with cardiorenal syndrome type 1. Subclinical acute kidney injury detected by NGAL was found to increase the risk of adverse outcomes, such as need for renal replacement therapy, hospital mortality, and duration of hospital stay, even in the absence of a diagnostically significant increase in serum creatinine [32].

Any decrease in subclinical acute kidney injury is therefore likely to be beneficial. In the long term, it may result in a small increase in GFR, which may be beneficial for the remaining donor function, and reduced haemodynamic stress on the donated kidney may potentially result in greater longevity of the allograft. Therefore optimisation of perioperative fluid management is likely to have a protective role.

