### Power Calculation to Determine Sample Size

Based on the observational pilot data discussed above, which demonstrated a 50% incidence of day 1 subclinical acute kidney injury in patients receiving <1000 ml of intravenous fluids and a 20% incidence of acute kidney injury (AKI) in patients receiving >2500 ml of intravenous fluids, we anticipate that 39 patients would be required in each arm to detect a similar magnitude of difference with 80% power and a significance level of 0.05. Allowing for 10% attrition, we intend to recruit a total of 86 patients.

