### Statistical Analysis

Descriptive statistics will be used to describe continuous variables. Results for continuous variables will be reported as mean (+/− standard deviation) or median (interquartile range). The primary outcome, proportion of patients in each group with subclinical acute kidney injury, will be compared using a chi-square test and 95% confidence intervals for the difference in proportions.

If the data for continuous variables follow a Normal distribution, the variables will be compared using a Student’s *t*-test. If data are found to not be Normally distributed, a Mann Whitney *U*-test will be used. Analysis will be performed on an intention-to-treat basis.

Study reporting will be in accordance with the CONSORT guidelines.

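### Donor eGFR is compared after donation without its pre-donation value, which is not on the data list: a valid comparison that gives up precision

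*Protocol article*

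**What the plan says.** The Secondary Outcomes section of the protocol article names donor serum creatinine and eGFR on the first four postoperative days, at six weeks and at one year. They form one item in a list that is not ranked. Table 1, under Data Collection, gives the matching entry: "Donor eGFR: days 1–4, week 6 and 1 year". Every one of these times is after nephrectomy. No other row of the table holds a donor creatinine or eGFR from before donation; the demographic row stops at age, gender, ethnicity, weight and body mass index.

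Other markers are treated differently. The same table lists donor NGAL and BNP on the day before surgery and immediately before it, and a baseline NGAL for recipients. Secondary Outcomes defines the NGAL outcomes as changes from baseline, but does not define donor eGFR in that way.

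The Statistical Analysis section sets one rule for continuous variables. If they are Normally distributed, "the variables will be compared using a Student’s" t-test; otherwise a Mann-Whitney U test is used. It mentions no covariate.

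The Pilot Data section explains why later renal function is of interest, in a statement about GFR (the quote stops just before that word): "Any decrease in subclinical acute kidney injury is therefore likely to be beneficial. In the long term, it may result in a small increase in". The section also reports an inverse correlation in the pilot between the rise in NGAL and eGFR six weeks after donation.

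**The concern.** A donor's eGFR after nephrectomy depends in part on the eGFR before it. An unadjusted comparison of post-donation values leaves that between-donor variation in the error term. A model with the pre-donation value as covariate removes the part that it explains.

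What is at stake is precision for a secondary outcome that the rationale leans on. The article argues for NGAL as a marker partly because it relates to later renal function, and the effect it hopes for on GFR may be small. The trial is sized for a binary NGAL outcome, so any eGFR comparison has to work with about 39 donors per arm. Available precision is worth having there, particularly as the baseline value is normally produced by the donor work-up.

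**Working it through.** **The plan's own figure.** The Power Calculation section assumes "50% incidence of day 1 subclinical acute kidney injury in patients receiving <1000 ml of intravenous fluids" against "20% incidence of acute kidney injury (AKI) in patients receiving >2500 ml of intravenous fluids", "with 80% power and a significance level of 0.05". With a two-sided test, pooled variance under the null and no continuity correction:

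n = [1.960 × √(2 × 0.35 × 0.65) + 0.842 × √(0.50 × 0.50 + 0.20 × 0.80)]² / 0.30² = (1.322 + 0.539)² / 0.09 ≈ 38.5, which rounds up to 39 per arm.

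This agrees with the article: "we anticipate that 39 patients would be required in each arm". Adding 10% gives 78 × 1.10 = 85.8, hence the stated 86. The sample size reproduces and is not in question here; 39 per arm is carried forward.

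**Inputs for the eGFR comparison.**
- n = 39 per arm, two-sided significance level 0.05, 80% power. The figures are from the Power Calculation section; two-sided is inferred because it reproduces the stated n.
- eGFR standard deviation: not given, so results are in SD units of post-donation eGFR.
- Correlation r between pre- and post-donation eGFR: not given. It is an assumption, shown from 0.3 to 0.8.

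**Unadjusted comparison.** Detectable difference = (1.960 + 0.842) × √(2/39) = 2.802 × 0.2265 = 0.63 SD. Power for a difference of 0.5 SD is 60% (normal approximation).

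**Adjusted comparison (ANCOVA).** Residual variance is multiplied by 1 − r², so the detectable difference is 0.634 × √(1 − r²). The equivalent unadjusted trial has 39 / (1 − r²) donors per arm.

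| r | Variance removed (r²) | Detectable difference, 80% power | Power for 0.5 SD | Equivalent unadjusted n per arm |
|---|---|---|---|---|
| none (unadjusted) | – | 0.63 SD | 60% | 39 |
| 0.3 | 9% | 0.61 SD | 64% | 43 |
| 0.5 | 25% | 0.55 SD | 72% | 52 |
| 0.6 | 36% | 0.51 SD | 79% | 61 |
| 0.7 | 49% | 0.45 SD | 87% | 77 |
| 0.8 | 64% | 0.38 SD | 96% | 108 |

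If all 86 donors are followed (43 per arm), the detectable difference goes from 0.60 SD unadjusted to 0.52 SD at r = 0.5 or 0.43 SD at r = 0.7.

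**Change score as an alternative.** If the spread is equal before and after donation, the variance of a change is 2(1 − r) times that of a single value: 1.40 at r = 0.3, 1.00 at r = 0.5 and 0.60 at r = 0.7. The ANCOVA multipliers are 0.91, 0.75 and 0.51. A change score is therefore worse than no adjustment below r = 0.5 and worse than ANCOVA throughout this range.

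**The case against.** The strongest reply is that this is an omission from a condensed article. The full protocol, case report form and analysis plan are not shown, and a baseline laboratory field or a covariate could appear in any of them. The sentence introducing Table 1 does not claim a complete list, and the Data Collection section names laboratory results as a source. This stands in part. A reader might infer that pre-donation eGFR will be unavailable; the article shows only that it is unlisted. What remains is that the article lists the eGFR times, lists baselines for other markers, and states a test without covariates for continuous variables. That the test would be run on raw post-donation values is the natural reading of these sections together, though no sentence says so outright.

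A second reply is that the analysis contains no error. This is correct. A reader might infer bias, or that a chance baseline imbalance could pass for a treatment effect. In a randomised trial the unadjusted test is unbiased and its type I error already allows for chance imbalance. Only precision is lost.

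A third reply is that adjustment will not make a small effect detectable. This also stands. If small is taken to mean 0.2 SD (an assumption), power at 39 per arm rises only from about 14% to about 23% at r = 0.7. The Background itself warns that eGFR is insensitive to limited damage and that nephrectomy and compensatory hypertrophy may mask subtle effects. Adjustment does not remove that masking. Equally, without an SD or an expected difference, the article cannot support a claim that baseline spread would overwhelm any effect.

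Finally, one might extend the point to recipient eGFR with the same gain. The range of r used here is assumed for one person before and after donation, and cannot be carried over to a donor's baseline and a recipient's eGFR.

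**Conclusion.** The point holds as one of efficiency. As the article is written, donor eGFR would be compared without its pre-donation value, and that value is not a listed study item. The comparison is valid but less precise than a simple alternative.

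The size of the gain rests wholly on the assumed r: slight at 0.3, material from about 0.5 upward. The calculation also assumes a roughly linear relation between pre- and post-donation values and uses a normal approximation. Correlation may differ between the early postoperative days, six weeks and one year, so the gain may differ by visit.

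Donor eGFR should not be read as a key secondary outcome, since the article does not rank the list. The primary outcome, its analysis and the sample size are untouched. This is a worthwhile and cheap improvement to a secondary outcome, not a flaw that threatens the trial's conclusions.

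**What to change.** Add pre-donation serum creatinine and eGFR, taken from the existing work-up record, to the donor data in Table 1. In the Statistical Analysis section, state that post-donation donor eGFR will be compared by ANCOVA with the pre-donation value as covariate, or by one repeated-measures model across the follow-up times with the same covariate. This replaces the unadjusted t-test or Mann-Whitney test for that outcome and is preferable to a change score.

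The cost is one data field, assuming the work-up value is on file, and one sentence of analysis text. No extra visit or change in sample size is needed. If the unseen full protocol or analysis plan already provides for this, it is enough to bring the article's wording into line with it.

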### Data Management

Data will be entered on a patient-by-patient basis into a computerised password-protected database on a computer within the Department of Renal Transplantation by an investigator blinded to the study group allocation. Patients will be identified by their study number only. After data analysis has been performed, it will be combined with the randomisation code and the nature of each patient’s perioperative fluid regimen will be revealed. This will be performed in accordance with the Data Protection Act. A case report file will be created for each patient. These will be archived in a locked facility and kept for a period of 3 years.

### Statistical Analysis

Descriptive statistics will be used to describe continuous variables. Results for continuous variables will be reported as mean (+/− standard deviation) or median (interquartile range). The primary outcome, proportion of patients in each group with subclinical acute kidney injury, will be compared using a chi-square test and 95% confidence intervals for the difference in proportions.

If the data for continuous variables follow a Normal distribution, the variables will be compared using a Student’s *t*-test. If data are found to not be Normally distributed, a Mann Whitney *U*-test will be used. Analysis will be performed on an intention-to-treat basis.

Study reporting will be in accordance with the CONSORT guidelines.

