### NGAL as a Biomarker of Subclinical Acute Kidney Injury

NGAL is a small 25 kDa protein of the lipocalin family, and was first identified by transcriptome analysis of the murine model, investigating the early induction of gene expression after renal ischaemia. Its expression was found to be upregulated in tubular cells after ischaemic injury [24]. NGAL levels have been shown to increase in both blood and urine in response to subclinical acute kidney injury [23, 25].

In an evaluation of 125 specimens from healthy individuals using the Alere Triage® CardioRenal Panel, it was found that the 95th percentile upper limit was 153 ng/mL. A study to determine the clinical utility of this compared the NGAL level of 494 plasma samples from patients in intensive care with the standard RIFLE criteria for acute kidney injury. AUC was 0.83 and a positive test threshold of 150 ng/mL yielded a sensitivity of 0.86 and specificity of 0.62 [26]. It was therefore shown to be a sensitive marker of disease.

There has been wide variation in reports of the diagnostic accuracy of NGAL, including variation in the specificities reported. This may be in part as a result of the different populations studied. NGAL is also produced by activated neutrophils and therefore may be raised in infection or inflammation [24, 25]. Plasma NGAL levels have been shown to be raised in septic ICU patients without acute kidney injury, and therefore plasma NGAL should be used with caution in this population [27]. As our population of interest is healthy, studies looking at populations outside a critical care setting are likely to be more generalizable to our population.

Other studies, using the point of care Triage^®^ NGAL Device, have demonstrated superior diagnostic accuracies. For example, 2-h plasma NGAL measurement of 120 children who underwent cardiopulmonary by-pass obtained AUC of 0.96 and the same AKI threshold of 150 ng/ml yielded a sensitivity 0.84 and specificity of 0.94 [28]. Several other studies have also confirmed the usefulness of these bedside NGAL assays in the clinical setting [29]. Therefore, conclusions drawn from previous studies support the diagnostic accuracy of this method.

In the living donor population, Yoon et al. demonstrated that perioperative plasma NGAL in living donors correlates with 6 month donor eGFR. This correlation was found to be strongest using plasma NGAL at 1 week post-operatively, but a correlation was found at all time points [30].

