### Primary Outcome

The primary outcome will be the incidence of donor acute kidney injury (as defined by plasma NGAL >153 ng/ml) on day 1 post-operatively.

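### The primary chi-square is valid but leaves the donors' day −1 NGAL unused; adjusting for it costs nothing and may add power, and a new-cases sensitivity analysis is needed alongside

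*Protocol article*

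**What the plan says.** The Primary Outcome section defines the endpoint as "incidence of donor acute kidney injury (as defined by plasma NGAL >153 ng/ml) on day 1 post-operatively". No condition is placed on the value before surgery. The Statistical Analysis section then states: "The primary outcome, proportion of patients in each group with subclinical acute kidney injury, will be compared using a chi-square test", with a 95% confidence interval for the difference in proportions. No covariate is named.

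Table 1 in Data Collection lists "Donor NGAL and BNP (4 measurements): preoperative (day −1), immediately preoperative (day 0"), followed by two postoperative samples. The infusion runs from midnight to 8 am before surgery, so the day −1 sample is read here as taken before it. Change in donor NGAL from baseline to day 1 is the first secondary outcome. As a continuous variable it would be compared by t-test or Mann-Whitney test.

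On the origin of the cut-off, the NGAL section of the Background says of 125 healthy specimens that "it was found that the 95th percentile upper limit was 153 ng/mL". The Exclusion criteria cover only open surgery and lack of consent, so a donor already above 153 ng/ml can enter.

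**The concern.** A pre-treatment measurement of the outcome variable itself is a natural covariate. If it predicts the day-1 value, leaving it out of the primary model forgoes precision that is already paid for. That matters in a small trial. The sample size rests on a 30-point difference from a non-randomised pilot series of 20 donors, and the Discussion says that a finding of no difference could lead to donors being admitted only on the morning of surgery. If the true effect is smaller than the pilot suggested, a missed effect could change practice.

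The second issue is the label. The endpoint is called incidence but is measured as a state on day 1. Because the threshold is a healthy 95th percentile, some donors may be over it before anything is done to them. They count as injured if they are still over it on day 1.

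**Working it through.** **Inputs.** From Power Calculation to Determine Sample Size: "50% incidence of day 1 subclinical acute kidney injury in patients receiving <1000 ml of intravenous fluids", "20% incidence of acute kidney injury (AKI) in patients receiving >2500 ml of intravenous fluids", and "39 patients would be required in each arm to detect a similar magnitude of difference with 80% power and a significance level of 0.05"; 86 in total after 10% attrition. From the NGAL section: about 5% of healthy people lie above the cut-off. The day −1 to day +1 correlation is not in the documents, so it is assumed to be 0, 0.3, 0.5 or 0.7.

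**Step 1: the plan's own figure.** Two-sided 0.05, pooled variance, no continuity correction, mean proportion (0.5 + 0.2)/2 = 0.35:

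n = [1.96·√(2·0.35·0.65) + 0.8416·√(0.5·0.5 + 0.2·0.8)]² / 0.30² = 38.48, so 39 per arm.

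78 × 1.10 = 85.8, so 86. Both figures reproduce. Exact power of the uncorrected chi-square is 81.3% at 39 per arm for 50% versus 20%, and 85.5% at 43 per arm if nobody is lost. For 50% versus 30% at 39 per arm it is 44.4%.

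**Step 2: adding the baseline.** Trials were simulated with 39 per arm and correlated normal log NGAL at day −1 and day +1, with the day-1 event rates held at the stated values. The chi-square was compared with the likelihood-ratio test for arm in a logistic regression that also contains baseline log NGAL. There were 2,000 trials per row for 50% versus 20% (Monte Carlo error about 1 point).

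| Assumed correlation | Chi-square, 50% vs 20% | Adjusted | Gain (points) | Gain for 50% vs 30% (points) |
|---|---|---|---|---|
| 0 | 83% | 83% | about 0 | about 0 |
| 0.3 | 83% | 85% | about 2 | about 2 |
| 0.5 | 81% | 87% | about 6 | about 7 |
| 0.7 | 82% | 93% | about 11 | about 16 |

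For 50% versus 30%, adjusted power was about 44 / 46 / 51 / 61%. With no treatment effect, rejection rates for the two tests lay between 3.9% and 6.1% across the settings run, so neither departs materially from 5%. At the design rates about 39 × 0.5 + 39 × 0.2 = 27.3 events are expected, enough for a model with two terms.

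**Step 3: donors above the cut-off at entry.** If donors resemble the healthy reference sample, 0.05 × 86 = 4.3, or about 4 donors and 2 per arm. Take the extreme case in which all of them stay above 153 ng/ml on day 1.

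- If the pilot rates already include such donors, the rates of new cases among the rest are (0.50 − 0.05)/0.95 = 47.4% and (0.20 − 0.05)/0.95 = 15.8%. The planned test keeps its stated power.
- If the pilot rates are new cases only, the observed rates become 0.05 + 0.95 × 0.50 = 52.5% and 0.05 + 0.95 × 0.20 = 24.0%. Power at 39 per arm, by the normal approximation, falls from 80.5% to 74.5%.

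The pilot used the same >153 ng/ml definition and the article mentions no baseline exclusion, so the first reading is the more natural one. The article does not settle it.

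**The case against.** The strongest reply is that nothing here is wrong. The test matches the sample size calculation, controls type I error and delivers its stated power. A reader might infer that the trial is underpowered or the test unsound; Step 1 shows neither. The attrition allowance also leaves some room if losses are small. This stands in full.

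Next, the gain rests on a correlation nobody has reported. Below about 0.3 it is negligible, and the simulation's normal, linear structure favours adjustment. The article gives some reason to expect a modest correlation: about 5% of healthy people exceed the cut-off, against about 50% of low-fluid donors after surgery, and NGAL also rises with inflammation. Day-1 status may owe more to the operation than to the starting level. This also stands, and it is why a range including zero is shown. At zero correlation, however, adjustment lost no power in the simulations.

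A reader might also infer that donors positive at entry, or chance imbalance in baseline NGAL, bias the result. They do not. Randomisation balances both on average, and chance imbalance is part of the sampling error that the chi-square already allows for. Nor would covariate adjustment solve the labelling problem: a donor above 153 ng/ml at both times remains an event in the logistic model, so that issue needs its own analysis.

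Finally, baseline NGAL is not ignored altogether, since a change score is a secondary outcome. That is correct, but it does not help the primary comparison.

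**Conclusion.** The point holds as a missed and free improvement to a sound primary analysis. For 50% versus 20%, the expected gain is between nothing and about 11 points of power as the assumed correlation goes from 0 to 0.7; for 50% versus 30% it is between nothing and about 16 points. A gain of 6 points or more needs a correlation of about 0.5. These figures assume normal log NGAL, a linear baseline effect and 39 analysed donors per arm.

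The labelling point holds separately and is small: about 4 of 86 donors if the 5% figure carries over, and only those still above the cut-off on day 1. It affects how the event proportions are described, not the validity of the comparison between arms. Whether it costs any power against the plan depends on what the pilot rates contain, which the article leaves open.

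**What to change.** Before unblinding, replace the primary analysis paragraph so that it states:

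- Primary: logistic regression of day-1 NGAL >153 ng/ml on randomised arm and log(day −1 NGAL), reported as a marginal (standardised) risk difference with 95% CI.
- Sensitivity 1: the unadjusted chi-square and difference in proportions as now planned.
- Sensitivity 2: new cases only, comparing arms among donors at or below 153 ng/ml on day −1, with the number above it at entry reported by arm.
- Baseline: the day −1 sample only, taken before the infusion and preferably before the allocation envelope is opened. Allocation also falls on the day before surgery, the Intervention Group section attaches the day −1 label to the infusion period too, and Table 1 does not say which of the two preoperative donor samples is the baseline. The immediately preoperative day 0 sample should not serve, because it follows the infusion window.

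The cost is one paragraph. No additional samples, patients or change to the sample size are needed.

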### Intra-operative management

All patients will receive standard anaesthetic care and monitoring. Additionally, in order to obtain key haemodynamic measurements, such as cardiac index (CI), systemic vascular resistance index (SVRI) and stroke volume index (SVI) measurements, the use of a non-invasive cardiac output monitor will be required. The NICCOMO^™^ bioimpedance system (Medis, Germany) will be used—a novel and totally non-invasive monitor which employs impedance cardiography to measure cardiac output. It does so by measuring electrical signals produced by changes in the volume and velocity of the blood in the thoracic aorta. This NICCOMO system is complemented by another device—the CNAP^™^ Monitor 500 (CNSystems, Austria). The CNAP Monitor employs the volume-clamp method of Penaz to measure non-invasive arterial blood pressure continuously via two small inflatable cuffs applied to the fingers of one hand. The cardiac output monitor will be attached to the patient shortly after the induction of anaesthesia and will remain in situ throughout the surgical procedure. It will be removed at the end of the operation before the patient is transferred to the recovery room. The anaesthetist will be blinded to the results of the cardiac output monitor.

The cardiovascular response to a single 500 ml fluid challenge will be assessed following the induction to anaesthesia. Cardiovascular parameters with be recorded, then a “stat” 500 ml fluid challenge will be administered and cardiovascular parameters recorded again. Again, the anaesthetist will be blinded to the results of this challenge.

Additionally a single 5 ml sample of venous blood will be obtained from the donor renal vein immediately after retrieval and immediately after implantation to assess the immediate impact on biomarkers of AKI.

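### The single t-test or Mann-Whitney rule for continuous outcomes makes no baseline adjustment and fits poorly the serial secondary outcomes that have no named time point or summary

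*Protocol article*

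**What the plan says.** Under Statistical Analysis, the protocol article fixes one two-branch rule for continuous variables. The first branch reads "If the data for continuous variables follow a Normal distribution, the variables will be compared using a" Student's t-test. The second reads "If data are found to not be Normally distributed, a Mann Whitney" U-test. The branch is chosen from the observed distribution. No covariate, repeated-measures model or summary measure is mentioned. The primary outcome is binary and handled separately: it "will be compared using a chi-square test and 95% confidence intervals for the difference in proportions".

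Several continuous secondary outcomes are series:

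- Donor creatinine and eGFR are listed under Secondary Outcomes for each of days 1 to 4, week 6 and 1 year.
- Table 1 (Data Collection) has "Donor NGAL and BNP (4 measurements): preoperative (day −1), immediately preoperative (day 0), immediately postoperative (day 0), postoperative (day +1" for the donor and "Recipient NGAL (3 measurements): preoperative (baseline), immediately post-operative, postoperative (day +1" for the recipient.
- Under Intra-operative management, the cardiac output monitor is attached shortly after induction and "will remain in situ throughout the surgical procedure".

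Secondary Outcomes names one contrast for donor NGAL, the day 1 change from baseline. It names no time point or summary for donor renal function, BNP, recipient NGAL or haemodynamics.

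**The concern.** A t-test and a Mann-Whitney test each compare one value per person between two arms. Where an outcome has several values per person and no contrast is named, the rule does not say what is being compared. The natural literal reading is a test at each time. That gives several correlated answers for one outcome and lets the test, and with it the quantity compared, change from one visit to the next. Where a pre-intervention value exists, the rule leaves it out of the analysis except where the outcome is itself defined as a change.

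These outcomes matter to the argument of the trial. The Discussion asks whether a haemodynamic benefit carries through to less subclinical injury, and the Pilot Data section links such injury to later donor GFR. With no named contrast, a favourable time point could be singled out once the data are seen. With about 39 donors per arm there is also little precision to spare.

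**Working it through.** **1. The plan's own figure.** Inputs from Power Calculation to Determine Sample Size: 50% against 20%, "with 80% power and a significance level of 0.05" (taken as two-sided), 1:1 allocation. The mean proportion is 0.35, so

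n = [1.960·√(2·0.35·0.65) + 0.842·√(0.5·0.5 + 0.2·0.8)]² / 0.30² = (1.322 + 0.539)² / 0.09 ≈ 38.5, or 39 per arm.

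With 10% added, 39 × 1.1 = 42.9, rounded to 43 per arm and 86 in total. The stated figures reproduce and are not in dispute.

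**2. Which outcomes lack a contrast.**

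| Outcome | Times collected | Contrast named |
|---|---|---|
| Donor NGAL | 4 | Yes: day 1 change from baseline |
| Donor BNP | 4 | No |
| Recipient NGAL | 3 | Change from baseline, time not named |
| Donor creatinine, eGFR | 6 each | No |
| Haemodynamics (at least 5 variables) | Monitored through surgery; number of readings not stated | No |

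**3. False positives if every visit is tested at 0.05.** For independent tests the chance of at least one is 1 − 0.95^k: 26% for k = 6 and 46% for k = 12 (creatinine and eGFR together). For correlated tests, take z_j = √r·u + √(1 − r)·e_j with u and e_j standard Normal, and find P(max |z_j| > 1.96) by simulation (200,000 draws). The documents give no r, so a range is shown.

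| r | 6 tests | 12 tests |
|---|---|---|
| 0.3 | 24% | 40% |
| 0.5 | 21% | 32% |
| 0.7 | 16% | 23% |
| 0.8 | 14% | 19% |
| 0.9 | 11% | 13% |

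One pre-named contrast per measure keeps 5% for that measure. No such count can be made for haemodynamics, because the number of readings is not given.

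**4. Precision for donor NGAL.** Assume equal variance at baseline and day 1, and correlation r between them. Relative to the variance of the day 1 value alone, a change score has 2(1 − r) and analysis of covariance has 1 − r². Their ratio is (1 − r²)/[2(1 − r)] = (1 + r)/2.

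The smallest difference detectable with 80% power at 39 per arm is (1.960 + 0.842)·√(2/39) = 0.63 SD for an unadjusted single value. Multiplying by the square root of each relative variance gives:

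| r | Change-score t-test | Analysis of covariance | Variance ratio |
|---|---|---|---|
| 0.3 | 0.75 SD | 0.61 SD | 0.65 |
| 0.5 | 0.63 SD | 0.55 SD | 0.75 |
| 0.7 | 0.49 SD | 0.45 SD | 0.85 |
| 0.8 | 0.40 SD | 0.38 SD | 0.90 |

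The covariance analysis is thus 10% to 35% lower in variance over this range.

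**5. What can serve as a baseline.** The Intervention Group section puts the fluid between midnight and 8 am before surgery. The day −1 NGAL and BNP samples are taken here to precede it. The haemodynamic monitor goes on only after induction, so its first reading follows the intervention. Table 1 lists no preoperative donor eGFR.

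**The case against.** The strongest reply is that testing at every visit is inferred. The section says only that variables will be compared, and a t-test on a well-chosen summary measure would satisfy it. Choosing that summary is commonly left to an SAP, and this is a condensed article. This stands in part: the article does not prescribe per-visit testing, and the percentages in step 3 are conditional on it and on any one significant visit being read as a finding. It does not dispose of the point. A method is stated for all continuous variables, without baseline adjustment and with a data-driven switch, and a better one is available from data already being collected.

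Four stronger readings are tempting and are not supported:

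- A reader might infer that ignoring within-donor correlation makes the tests invalid. A between-arm test at one visit uses one value per donor and keeps its 5% level. Nothing says that repeated values will be pooled as independent.
- A reader might infer that no continuous outcome has a single answer. Donor NGAL does, and a t-test on its change score is valid.
- A reader might credit a repeated-measures model with a large gain from averaging: a mean of days 1 to 4 has (1 + 3r)/4 times the variance of one day, or 0.925, 0.775 and 0.625 at r = 0.9, 0.7 and 0.5. That is a different quantity from eGFR at 1 year. At a single visit with complete data and no baseline covariate, such a model is essentially as precise as the t-test.
- A reader might want haemodynamics adjusted for the post-induction reading. The Fluids in Transplant Optimization section proposes that fluid maintains cardiac output, so that reading may already carry the effect, and adjusting for it could remove part of what is under study.

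**Conclusion.** The point holds for secondary outcomes only. The stated rule suits poorly donor creatinine and eGFR, BNP, recipient NGAL and haemodynamics, because each is a series with no named time point or summary. If each of six eGFR visits were tested, the chance of at least one false positive would be about 11% to 24%, under an assumed equal correlation of 0.9 to 0.3 between visits. For donor NGAL the issue is precision alone: a 10% to 35% reduction in variance is available for an assumed r of 0.8 to 0.3, with day −1 taken as the baseline. All of these sizes rest on correlations that the article does not give. The primary chi-square analysis and the 39 per arm (86 in total) stand.

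**What to change.** Replace the general rule for the serial outcomes with three statements.

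(a) Donor NGAL, donor BNP and recipient NGAL, on the log scale if skewed: analysis of covariance or a repeated-measures model adjusted for the value already collected before the intervention (day −1 for donors) or before surgery (recipients). Report one pre-named contrast each, at day 1.

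(b) Donor creatinine and eGFR: one repeated-measures model per measure with one pre-named contrast, for example the difference at 1 year. Treat the other visits as supportive. Use a preoperative value as covariate only if it is recorded.

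(c) Haemodynamics: one pre-named summary per variable, for example the time-weighted mean during pneumoperitoneum, compared between arms without adjustment for the post-induction value.

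Leave the primary chi-square test and its confidence interval unchanged. The cost is a few sentences and modest extra modelling, with no new patients or measurements. The small downside is reliance on a model, which an unstructured covariance or a simple summary measure eases.
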